# Improving medication adherence among persons with cardiovascular disease through m-health and community health worker-led interventions in Kerala; protocol for a type II effectiveness-implementation research-(SHRADDHA-ENDIRA)

**DOI:** 10.1186/s13063-024-08244-0

**Published:** 2024-07-02

**Keywords:** Coronary artery disease, Factorial study design, Valvular disease, Arrhythmia, Heart failure, Implementation Research, Medication adherence, Morisky Medication Adherence Scale

## Abstract

**Background:**

Cardiovascular disease (CVD) is the leading cause of mortality worldwide, and at present, India has the highest burden of acute coronary syndrome and ST-elevation myocardial infarction (MI). A key reason for poor outcomes is non-adherence to medication.

**Methods:**

The intervention is a 2 × 2 factorial design trial applying two interventions individually and in combination with 1:1 allocation ratio: (i) ASHA-led medication adherence initiative comprising of home visits and (ii) m-health intervention using reminders and self-reporting of medication use. This design will lead to four potential experimental conditions: (i) ASHA-led intervention, (ii) m-health intervention, (iii) ASHA and m-health intervention combination, (iv) standard of care. The cluster randomized trial has been chosen as it randomizes communities instead of individuals, avoiding contamination between participants. Subcenters are a natural subset of the health system, and they will be considered as the cluster/unit. The factorial cluster randomized controlled trial (cRCT) will also incorporate a nested health economic evaluation to assess the cost-effectiveness and return on investment (ROI) of the interventions on medication adherence among patients with CVDs. The sample size has been calculated to be 393 individuals per arm with 4–5 subcenters in each arm. A process evaluation to understand the effect of the intervention in terms of acceptability, adoption (uptake), appropriateness, costs, feasibility, fidelity, penetration (integration of a practice within a specific setting), and sustainability will be done.

**Discussion:**

The effect of different types of intervention alone and in combination will be assessed using a cluster randomized design involving 18 subcenter areas. The trial will explore local knowledge and perceptions and empower people by shifting the onus onto themselves for their medication adherence. The proposal is aligned to the WHO-NCD aims of improving the availability of the affordable basic technologies and essential medicines, training the health workforce and strengthening the capacity of at the primary care level, to address the control of NCDs. The proposal also helps expand the use of digital technologies to increase health service access and efficacy for NCD treatment and may help reduce cost of treatment.

**Trial registration:**

The trial has been registered with the Clinical Trial Registry of India (CTRI), reference number CTRI/2023/10/059095.

## Administrative information

Note: the numbers in curly brackets in this protocol refer to SPIRIT checklist item numbers. The order of the items has been modified to group similar items (see http://www.equator-network.org/reporting-guidelines/spirit-2013-statement-defining-standard-protocol-items-for-clinical-trials/).

## Introduction

### Background and rationale {6a}

Cardiovascular disease (CVD) is the leading cause of mortality worldwide, and at present, India has the highest burden of acute coronary syndrome and ST-elevation myocardial infarction (MI) [1]. A key reason for poor outcomes is non-adherence to medication. The WHO has reported that non-adherence to drugs in chronic conditions is as high as 50%, and 30% of re-admissions are related to non-compliance to medication. In its 2003 report [2], WHO states that “increasing the effectiveness of adherence interventions may have a far greater impact on the health of the population than any improvement in specific medical treatment.”

A systematic review published in 2015 on adherence to medication had eleven studies from India reporting adherence rates (using pills taken, prescribed doses taken, changes, etc.) using Morisky Medication Adherence Score (MMAS) in the range of 0–51.2% [3–8]. The factors associated with non-adherence to medications were forgetfulness, difficulty in remembering, and stopping medication upon feeling better/worse.

Various interventions have been studied to increase medication adherence for cardiovascular disease in India. These include the use of combination therapy or polypill [9–11], use of community health workers (CHW) for simplified hypertension management with the aid of a smart-phone-based electronic decision support system [12], “task shifting” interventions to CHWs for CVD risk reduction through behavioral change [13], improving adherence to drugs, lifestyle changes, and clinical risk markers in patients of acute coronary syndromes [14, 15] and use of CHWs and doctors in primary health center (PHC) to assess CVD risk with clinical decision support being provided through an m-health platform by doctors sitting remotely [16]. Studies have also identified the use of mobile technology by health workers in resource-limited settings for health delivery improvement [17]. The different studies mentioned have looked at m-health or CHWs alone to improve adherence to medication, lifestyle changes, or as a platform for treatment, with varied results.

We measured adherence in 2064 patients of coronary artery disease (CAD) the ENDIRA cohort using the MMAS-8 in the year 2019. Our results revealed poor adherence to chronic care medications in CAD patients. On an average, only 2.8 of the mandated 4 drugs (beta blocker, ACE Inhibitor /ARB, statin, and anti-platelet) were being taken by patients regularly [18]. The mean value of MMAS was 4 out of a possible 8, reflecting poor adherence [19]. A study on the feasibility of an m-health intervention in the same cohort for the prevention and management of CAD revealed that the use and ownership of mobiles was 88% (2015), 92% were willing to receive mobile health advice [19], 70% preferred voice calls over SMS, 85.9% would send self-recorded blood pressure, weight, and blood glucose to a doctor or community health worker [19]. Given that the results of our study revealed poor adherence and that use of m-health for CVD was both acceptable and feasible, the obvious next step would be in trying to improve adherence using these resources.

### Objectives {7}

#### Primary objective

To assess the effectiveness of using m-health and community health worker-led interventions for improving adherence to drugs in patients with cardiovascular disease using m-health and community health worker intervention individually and in combination in comparison to control group.

#### Secondary objective

(2)To assess the effects of using the interventions (m-health and community health worker-led interventions) for improving adherence to drugs among heart disease patients on implementation outcomes such as acceptability and adoption.(3)To assess the cardiometabolic risk factors among first degree relatives of patients with heart disease

### Trial design {8}

It is a 2 × 2 factorial design trial applying two interventions individually and in combination with a 1:1 allocation ratio. Two interventions are applied individually and in combination: (i) ASHA-led medication adherence initiative comprising of home visits, and (ii) m-health intervention using reminders and self-reporting of medication use. This design will lead to four potential experimental conditions: (i) ASHA-led intervention, (ii) m-health intervention, (iii) ASHA and m-health intervention combination, (iv) standard of care.

## Methods: participants, interventions, and outcomes

### Study setting {9}

The study will be implemented in the ENDIRA (Epidemiology of Non-communicable Diseases in Rural Areas) cohort (n-114,064 individuals) which includes 2064 patients with heart disease in whom adherence to drugs for heart disease has already been assessed. The ENDIRA cohort is spread over 5 primary health centers consisting of 18 subcenters where the health details of all individuals have been recorded. In order to avoid contamination in the treatment allocation and its response, at least 10 km of distance among villages will be maintained and they will be clubbed into 4 groups.

The intervention will be implemented in Angamaly block consisting of five local self-government areas namely Mookkannoor, Kalady, Thuravoor, Karukutty, and Manjapra with a population of 18,638, 20,407, 20,475, 26,811, and 14,668 in Ernakulam district [20] in Kerala state, India, respectively.

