## Assignment of interventions: allocation

### Sequence generation {16a}

Allocation of intervention and sequence generation will be as follows. Codes will be randomly assigned to the four interventions (ASHA, m-health, ASHA + m-health, and control groups) namely A, B, C, and D. In the next step, randomization list will be generated using RANDOM ALLOC software. Eighteen subcenters will be randomized into 4 study groups (A, B, C, and D) using different permutations of ABCD. Each subcenter will be allocated random numbers ranging from 1 to 18 using random number generators and random shuffling of this number. Interventions will be allocation to the subcenters in the sequence of random shuffled numbers as per the randomization list.

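### The promised 10 km separation between villages is not carried into the allocation, which randomizes all 18 subcenters with no geographic restriction

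*Protocol article*

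**What the plan says.** Study setting {9} gives the only geographic safeguard in the article. To keep treatment in one place from affecting response in another, "at least 10 km of distance among villages will be maintained and they will be clubbed into 4 groups". It does not say between which villages the distance applies, whether any villages are left out as buffers, or whether the grouping comes before or after randomization.

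Sequence generation {16a} gives the only description of allocation: "Eighteen subcenters will be randomized into 4 study groups (A, B, C, and D) using different permutations of ABCD". The order comes from a shuffle: "Each subcenter will be allocated random numbers ranging from 1 to 18 using random number generators and random shuffling of this number". No distance, buffer or geographic stratum is mentioned.

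The 18 subcenters randomized are the whole cohort: "The ENDIRA cohort is spread over 5 primary health centers consisting of 18 subcenters". The abstract expects "393 individuals per arm with 4–5 subcenters in each arm", and it justifies the cluster design because "it randomizes communities instead of individuals, avoiding contamination between participants". Recruitment {15} places randomization after recruitment, and Concealment mechanism {16b} places it after the baseline assessment.

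**The concern.** The setting section states a property of the design, and the allocation section describes a procedure that does not produce it. A reader of the results would take it that participants in different arms live at least 10 km apart. Under the stated procedure, adjoining subcenters can be in different arms, and usually will be.

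This matters because avoiding contamination is the stated reason for randomizing clusters. The trial is open-label, and ASHAs, patients and outcome assessors are all unblinded. The primary outcome is a self-reported adherence score, and the planned difference is small: 0.4 units against a standard deviation of 1.8. Spillover of advice or reminders into a neighbouring arm would tend to shrink the differences between arms. If the report relies on a separation that was never imposed, a null or small effect could be misread.

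**Working it through.** **1. Arm sizes.** 18 subcenters over 4 arms is 18/4 = 4.5, which agrees with the abstract's 4–5 per arm. Permutations of ABCD give four complete blocks (4 × 4 = 16) plus two further allocations, so the arms have 5, 5, 4 and 4 subcenters. The allocation is restricted for arm balance, but not for geography.

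**2. How often two subcenters fall in different arms.** The shuffle makes every pair of subcenters equally likely to occupy any two positions in the list.
- All pairs: C(18,2) = 153.
- Same-arm pairs: C(5,2) + C(5,2) + C(4,2) + C(4,2) = 10 + 10 + 6 + 6 = 32.
- Probability of different arms: 1 − 32/153 = 121/153 = 0.791.

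This holds for neighbours as for any other pair, because location plays no part in the draw.

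**3. Whether village selection could supply the gap.** Participants are recruited and assessed at baseline before allocation. At enrolment nobody knows which nearby subcenter will be in another arm, so villages cannot be picked to lie 10 km from other-arm villages. A guarantee would need the enrolled villages of every subcenter to be 10 km from those of every other subcenter. The eligibility criteria contain no distance condition. There is also little slack: the target of 1,572 is 1,572/2,064 = 76% of the cohort patients recorded in Study setting {9} ("which includes 2064 patients with heart disease"). That share is only indicative, since eligibility also covers valve, rhythm and heart failure cases.

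**4. Whether mutual separation is plausible.** The article gives populations ("with a population of 18,638, 20,407, 20,475, 26,811, and 14,668") but no area.
- 18,638 + 20,407 + 20,475 + 26,811 + 14,668 = 100,999.
- For points at least d apart in a convex region of area A and perimeter P, the packing bound is N ≤ 2A/(√3·d²) + P/(2d) + 1. Here d = 10 km, with one point per subcenter.
- Circle, A = 990 km²: 11.43 + 5.58 + 1 = 18.0.
- 4:1 rectangle, A = 844 km²: 9.75 + 7.26 + 1 = 18.0.
- Highest density that still allows 18 points: 100,999/990 = 102 per km² (circle) and 100,999/844 = 120 per km² (rectangle).

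Range under assumed densities:

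| Assumed people per km² | Area (km²) | Most sites 10 km apart (circle to 4:1 rectangle) |
|---|---|---|
| 100 | 1,010 | 18–20 |
| 200 | 505 | 10–12 |
| 500 | 202 | 5–6 |
| 1,000 | 101 | 3–4 |

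The bound is lenient, because it treats each subcenter as a single point although it would hold on average 1,572/18 = 87 participants spread over some area.

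**The case against.** The strongest defence is that the two sections describe one design loosely. Elsewhere the protocol uses the word group for an arm, so the four groups are most naturally the arms. Distance is stated among villages, while the units randomized are subcenters, so separation might be sought by selecting villages. Nor is distance the only protection. Whole communities are randomized, the app's communication channel is blocked in clusters without m-health, and the ASHA component is delivered by home visit. Operational detail may sit in the full protocol.

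Much of this stands. The 79% is a consequence of any balanced four-arm allocation of 18 clusters; it does not measure contamination. The village-selection defence does not stand, because enrolment precedes allocation. A fuller document could explain how distance is handled, but the article states a specific property next to a specific procedure that does not deliver it.

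Three stronger readings are tempting, and the article does not support them:
- **Each arm is one geographic block, leaving no replication.** The abstract names the subcenter as the cluster with 4–5 per arm, Implementation {16c} assigns by subcenter, and the analysis uses cluster random effects. Nothing says that four pre-formed blocks are randomized.
- **The 10 km rule and the allocation cannot coexist.** Without an area or distances this is unproven; it depends on population density.
- **There is no protection against contamination.** The safeguards listed above remain.

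**Conclusion.** The point holds as a mismatch between a stated design property and the stated procedure. The 10 km separation has no counterpart in the allocation, and the order of recruitment, baseline and randomization closes the obvious route to achieving it. The 79% chance that two given subcenters differ in arm follows from the article's own figures, given arms of 5, 5, 4 and 4. The density ceiling of roughly 100–120 people per km² rests on assumptions: the listed population, a convex compact or moderately elongated area, and one point per subcenter. It makes full separation doubtful at higher densities but does not rule it out. The size of any spillover bias cannot be derived from the article.

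Validity under the 18-cluster design is not in question, and neither the sample size nor the mixed model depends on the 10 km statement. The correction should be made because the claim bears directly on how the results will be read.

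**What to change.** 1. State in Study setting {9} that each of the 18 subcenters is its own randomized cluster, and that the four groups are the four arms formed by randomization, not blocks formed beforehand.
2. Then take one of two routes. Either withdraw the 10 km statement or, if allocation has not yet been done, draw it only from lists that meet a stated, achievable minimum distance between subcenters of different arms. The article was published on 2 July 2024 and expected recruitment to end on 30 May 2024, so allocation may already have taken place. In that case only the first route is open.
3. Prespecify a sensitivity analysis of the primary outcome that excludes participants living within a fixed distance of a subcenter in another arm, with the distance chosen before outcome data are seen.

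**Cost.** Wording changes and one extra analysis. The stated protection against contamination becomes weaker, and the sensitivity analysis uses fewer participants and so is less precise. A distance-restricted list, if used, also reduces the number of admissible allocations.

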### Eligibility criteria {10}

The study samples will consist of adult community members with diagnosis of CAD, valvular disease, heart failure, and rhythm disorders in the target areas who provide informed consent.

#### Eligibility criteria

Diagnosed case of CAD who have received treatment for MI/STEMI/UA or diagnosed using a coronary angiogram or CT coronary angiogram or have undergone revascularization and are on medications.Other cardiovascular cases such as rhythm disorders, valve disorders, and heart failure identified as pumping disorders by the community will also be a part of the study. Male or female aged 18 years or more will be considered.Resident of village during the baseline survey.Has no plans to migrate in next 12 months from the date of initiation of intervention.

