#### Exclusion criteria

Persons who are bedridden and are unable to answer the questions.Pregnant or lactating mothersIndividuals with cognitive impairment

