## Baseline study

*Selection and training of team*: The team will deliver the training to the selected project coordinator and the field staff. Field staff (part-time) will be recruited by the investigators on the advice of village head and/or NCD clinic in-charge. He/she should be a member of community preferably the accredited social health activist with an interest in health care and community, willingness to learn, and leadership qualities. A strong commitment to work in the community will be identified as an important criteria for the selection of all the team members. After a sensitization session of the data collectors/field staff, they will be asked to prepare a list of persons with cardiovascular disease including coronary artery disease, valvular disease, arrhythmias, and heart failure. Hands on sessions to download the App and collect data will be provided.

In Phase 2, baseline evaluation will be initiated in the study areas after obtaining the ethics committee approval. Written informed consent will be obtained from the study participants. Participants will receive a participant information sheet (PIS) outlining the rationale for the study, details on interventions, the steps, and protocols to be followed throughout the study, potential side effects and risks, benefits, a confidentiality statement, the option to withdraw from the study at any time, and the investigators’ contact information. The baseline survey performed by ASHAs will be done through a survey app called SHRADDHA. The variables collected would include (1) basic demographic information, including age, income, gender, marital status, religion, and occupation; (2) lifestyle-related factors such as physical activity, tobacco use, and alcohol consumption, dietary factors intake of fruits and vegetables, cooking oil and red meats; (3) disease details including for diabetes, hypertension, dyslipidemia, stroke and CAD, COPD, and surgeries; and (4) current medications. Questions will be explained to each participant to help them get familiar with the contents, instructions for filling them out will be given, and the responses will be recorded. On the home visit, the Field staff/ASHA will also record height and weight, measure sugars with a glucometer, and take a photo of the most recent prescription. All of this will be recorded in the app. Glycosylated hemoglobin will also be measured among the cardiac patients with diabetes using the point of care device called Lumira Dx.

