## Data collection and management

### Plans for assessment and collection of outcomes {18a}

The primary outcome adherence will be measured by Morisky 8-item adherence questionnaire which has been validated in various countries including India and in various disease conditions. The eight-item Morisky Medication Adherence Scale (MMAS-8) is a structured self-report measure of medication-taking behavior that has been widely used in various cultures [25–27].It has a maximum score of 8.

The quality of life will be measured by the EuroQol five‐dimensions – 3‐level (EQ5D) which is a versatile quality of life (QOL) instrument with five dimensions (mobility, self‐care, usual activities, pain/discomfort, and anxiety/depression) and a visual analog scale. The questionnaire has also been found to be valid and reliable in various disease conditions including cardiovascular and cancer in India and neighboring countries [28, 29].Random blood sugar among the patient and family member will be measured by the ASHA as per standard methods using a glucometer. Blood pressure will also be measured using the electronic Blood pressure will be recorded with the OMRON HEM 7124 automatic blood pressure monitor (Shimogyo-ku, Kyoto, Japan) by measuring upper arm BP. A laboratory technician will measure Glycosylated Haemoglobin using the Lumira Dx point of care device.

Real-time data entry will be monitored, and wherever there are difficulties with using the app, support will be provided by the field coordinator.

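### The requirement to be on medication is attached only to CAD, so valve, rhythm and heart failure cases with no prescribed drug can enter although the MMAS-8 primary outcome has no meaning for them

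*Protocol article*

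**What the plan says.** The bulleted eligibility criteria treat the diagnoses in two separate sentences. The CAD sentence closes with the medication condition: "diagnosed using a coronary angiogram or CT coronary angiogram or have undergone revascularization and are on medications". The following sentence brings in the other cardiac diagnoses without one: "heart failure identified as pumping disorders by the community will also be a part of the study".

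Three other places could have supplied the condition, and none does:

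- The general statement under Eligibility criteria {10} asks for a diagnosis, adult age, residence in the area and consent: "adult community members with diagnosis of CAD, valvular disease, heart failure, and rhythm disorders in the target areas who provide informed consent".
- The exclusion criteria cover bedridden people who cannot answer, pregnancy or lactation, and cognitive impairment. Absence of prescribed treatment is not listed.
- The case-finding step under Baseline study is by disease only. Field staff are to "prepare a list of persons with cardiovascular disease including coronary artery disease, valvular disease, arrhythmias, and heart failure".

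Current medications are recorded at the baseline survey, and staff "take a photo of the most recent prescription", but these are baseline data and not entry conditions.

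The primary outcome (Outcomes {12}) is the Morisky score. Section {18a} says that the scale "is a structured self-report measure of medication-taking behavior", and section {20a} makes change in that score the primary dependent variable.

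**The concern.** An adherence score presupposes something to adhere to. A person with valve disease, a rhythm disorder or heart failure who has been prescribed nothing has no medication-taking behaviour to report. The interventions presuppose drugs in the same way: the home visits include a pill count and an explanation of drug classes, and the m-health arm sends reminders timed to doses. Such a person can neither supply the primary outcome nor respond to what is being tested.

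Two things can then happen. If no score is recorded, the evaluable sample is smaller than planned. Section {20c} leaves imputation open, so an undefined value could even be filled in as though it existed. If a score is recorded anyway, it cannot move for a reason related to the intervention, and the between-group difference shrinks. Because the lists are compiled locally, the share of such people may also differ between subcenters; nothing in the document allows that to be sized.

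**Working it through.** **Text.** Set side by side, the CAD sentence carries the medication condition and the sentence on other diagnoses does not. The general statement, the exclusions and the case-listing step do not extend it. This part of the point needs no arithmetic.

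**Inputs for the size.** From the protocol's sample size text: difference 0.4 units, SD 1.8, 238 per group before inflation, 10% attrition, 393 per group after inflation. Not stated: the design effect, the sidedness of the test, and the share *p* of participants without a prescribed drug. I take *p* = 5% to 20% purely for illustration.

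**The plan's own figures.**

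- Two-sided 5%, 80% power: n = 2(1.960 + 0.842)² × 1.8² / 0.4² = 318 per group. One-sided 5% gives 251. Neither is 238, and a multiplicity adjustment moves further away (424 at two-sided 0.05/3).
- 238 × 1.5 × 1.1 = 392.7, which rounds up to 393. A design effect of 1.5 is therefore implied. 393 × 4 = 1572 agrees with the stated total.

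**Starting power.** Evaluable per arm: 393 × 0.9 = 353.7, about 354. Divided by 1.5, the effective n is 235.8. SE = 1.8 × √(2/235.8) = 0.1658. Power = Φ(0.4/0.1658 − 1.960) = Φ(0.453) = 67%.

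**Case A: scores missing.** Evaluable n = 353.7(1 − p); difference and SD unchanged.

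**Case B: scores recorded with zero change.** The difference becomes 0.4(1 − p). The variance of change also falls, because a share *p* has no change at all. With SD 1.8 among those who can change and mean change m in an arm, the variance is (1 − p) × 1.8² + p(1 − p)m². I take m = 0 in control and 0.4 in the intervention arm. At p = 20% the variances are 2.592 and 2.618, SE = √(5.210/235.8) = 0.1486, and power = Φ(0.32/0.1486 − 1.960) = Φ(0.193) = 58%.

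**Case C: as B, but SD held at 1.8 for everyone.** Power = Φ(0.4(1 − p)/0.1658 − 1.960).

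| p | Evaluable per arm (A) | Power A | Difference (B, C) | Power B | Power C |
|---|---|---|---|---|---|
| 0% | 354 | 67% | 0.40 | 67% | 67% |
| 5% | 336 | 65% | 0.38 | 65% | 63% |
| 10% | 318 | 63% | 0.36 | 63% | 58% |
| 15% | 301 | 60% | 0.34 | 60% | 54% |
| 20% | 283 | 58% | 0.32 | 58% | 49% |

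If both arms also had a background change of 0.4 units, case B would run from 65% to 57%, so the result is not sensitive to that choice.

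**The case against.** The best defence is that the intent is plain. The primary objective is to improve adherence to drugs, visits include a pill count, and prescriptions are recorded at baseline, so medicated patients were surely meant and untreated people would be visible before allocation. That stands as an account of intent, and this may be only a drafting gap. It does not change what field staff in 18 subcenters are told to apply.

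A second objection is that the untreated share may be trivial. That also stands as far as it goes: the document gives neither the share of non-CAD cases nor the share untreated. The 5%-20% range refers to all participants, so an overall 20% would need a still higher untreated share among non-CAD cases if CAD cases are all medicated. The previous adherence survey does not settle it. The Background describes its 2064 members as CAD patients, while Study setting calls them patients with heart disease.

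Four stronger readings are tempting and should not be drawn:

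- *Power falls to 63%-49%.* This is case C. It needs an SD of 1.8 that is unaffected by people whose score cannot change. The primary variable is change, and zero changes shrink its variance. The protocol does not say whether 1.8 is the SD of the score or of change.
- *Eligibility explains the whole gap from 80%.* The 67% starting point arises because 238 per group does not follow from the stated inputs. That is a separate matter.
- *Non-CAD cases need no proper diagnosis.* The general statement requires a diagnosis for all four conditions, and the phrase about the community most naturally explains heart failure in lay terms.
- *Untreated people would get the top score.* The scale's items and a scoring rule for such people are not in the document.

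**Conclusion.** The point holds on the text. As written, the criteria admit valve, rhythm and heart failure cases with no prescribed drug, and for them change in MMAS-8 has no meaning. This is a stated eligibility rule that gives a worse trial if followed literally, so it should be corrected in the protocol.

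Its size is modest and uncertain. With an assumed 5%-20% of such participants, pairwise power drops by about 2 to 10 percentage points, from about 67% to about 65%-58%, under either missing or unchanging scores. This rests on a difference of 0.4, SD 1.8, a back-solved design effect of 1.5, 10% attrition and a two-sided 5% test without multiplicity adjustment. If nobody without a prescription enters, nothing is lost. The textual defect does not depend on these figures.

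**What to change.** In the eligibility criteria, replace the CAD-only phrase with one condition that applies to every diagnosis: at least one long-term cardiovascular medicine prescribed at baseline, whether or not it is currently being taken. Establish it from the medication list and prescription photo already collected at baseline, or from the medical record, for which section {26b} already seeks consent.

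The wording should turn on being prescribed a medicine and not on being on one. The Background names stopping medication as a factor in non-adherence, so people who were prescribed drugs and stopped are among those the trial aims to help. A rule based on current use, or one that accepts only a prescription photo, could exclude them.

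For people already enrolled, define the primary analysis set by the same baseline criterion and fix it before subcenters are allocated. Sections {15} and {16b} place allocation after recruitment and baseline assessment, so this is not a post-randomization exclusion.

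The cost is one line in the criteria and one in the definition of the analysis set, with no new data collection. The downside is slightly fewer eligible participants.
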